## Abstract

**Background:**

This research program aims to investigate the implementation and effects of a theoretically promising prevention method. It is being developed in a European research collaboration within a Comenius project (2012–2015) between 6 European universities (in Malta, Italy, Greece, Croatia, Portugal and Sweden) with the purpose of enhancing European children’s resilience.

**Methods/design:**

RESCUR in Sweden consists in a RCT study of the *Resilience Curriculum* (*RESCUR*) that is taking place in Sweden 2017–2019. The study is being performed by Junis, IOGT-NTO’s Junior Association, part of IOGT International, in conjunction with researchers at Göteborg, Umeå and Stockholm universities, and is being funded by the Public Health Agency of Sweden.

Around 1000 children of the ages 7–12 will, through their schools and associations, or via groups in social services, be acquainted with the material. Children will learn and practice mindfulness, storytelling, group discussions and much more, all designed to strengthen protective factors and increase their resilience. The program also involves parents, who are taking part in the work to reinforce children’s protective factors.

Based on the work with groups of children, an effectiveness study including children aged 7–12 in school classes, with randomized and controlled pre- and post-measurements, self-rating questionnaires and group observations is being performed. The program will also be implemented in a non-governmental organization and in groups in social services. The study also investigates forms of implementation.

**Discussion:**

The design of the study will enable the researchers to answer five research questions by using a mixed-methods approach. Implementation will be studied, which is a necessary prerequisite for an effect study. Moreover, the research procedure has been tailored to the target group, with age-appropriate measures as well as multiple informants, which will produce high-quality data for analysis. A special ethical challenge is the study of young children, and efforts to give children a voice have been included in the program. This project is regarded as having good potential to benefit children in general, and particularly children in vulnerable positions.

**Trial registration:**

National Institute of Health, ClinicalTrials.gov identifier NCT03655418. Registered August 31, 2018.

## Background

A resilience curriculum to foster the psychosocial development of children in early and primary education has been developed as a direct response to the current social and economic situation in Europe. The curriculum seeks specifically to promote the academic, emotional and social learning of children who may be at risk of early school-leaving, absenteeism, school failure, social exclusion and mental health problems, by providing them with key tools to overcome disadvantages and obstacles in their development whilst making use of their strengths [1, 2].

### Top of form

This research program aims to investigate the implementation and effects of a theoretical promising method developed in a European research collaboration within a Comenius project (2012–2015) between 6 European universities (in Malta, Italy, Greece, Croatia, Portugal and Sweden). The program has the purpose of enhancing European children’s resilience [1, 2]. RESCUR in Sweden consists in a RCT study of the *Resilience Curriculum* (*RESCUR*) that is taking place in Sweden 2017–2019. The study is being performed by a non-governmental organization (Junis, IOGT-NTO’s Junior Association, part of International Organization of Good Templars International) and researchers at Göteborg, Umeå and Stockholm universities. The focus is on children in general as well as children exposed to different social risks. They may be refugees or relatives of a person with harmful use of alcohol. In the Swedish study, we are also studying the method among children in general. It is intended that the study’s findings are will be compared with those of other impact studies planned in the other European RESCUR partner countries, such as Portugal and Italy.

### Resilience

The concept of resilience is central, and refers to the ability to cope with crises, changes and stressors without breaking down [1]. Most children who are exposed to stressful environments will develop positively despite the odds against them. These children, e.g., children of schizophrenic parents who did not get ill, were previously described as invulnerable, [3, 4]. Research has shown that a key factor is resilience, where the interaction between risk and protective factors results in different development patterns [5–7]. The approach means a shift from a disease or deficiency model to a more optimistic and salutogenic focus on strengths, assets and adaptive functioning, which gives new impetus to the development of preventive and therapeutic interventions [8].

Resilience is generally defined as a process by which individuals exhibit adaptive functioning despite encountering significant difficulties [9–14]. The term is used with reference to a positive outcome despite experiences of difficulties, continued positive or effective functioning in adverse circumstances, or recovery after a significant trauma [15]. It was in the 1980s that the dynamic nature of these development processes was identified [14–18].

The concept of resilience has been linked to positive development and good living patterns in longitudinal studies [8, 16, 19–21]. The characteristics of the individual are significant, as are the family environment and the larger social contexts [21, 22]. Risk factors may be attitudes, beliefs, behaviors or environmental conditions that adversely affect development. Poverty is, for example, a negative factor that is important for children’s health and development [7, 21, 23]. A review of longitudinal and cross-sectional studies has identified ten protective factors that play a role in resilience during childhood [24]: (1) effective parenting, (2) affiliation with other competent adults, (3) openness to other persons, especially adults, 4) good intellectual capacity, 5) a talent or skill worthy of the child and others, 6) self-reliance, self-esteem and hopefulness, 7) religious belief, 8) good socio-economic conditions, 9) a good school and other resources in the local community, and (10) good luck or success.

To capture these developmental processes, more system-based, ecological and transactional models have been developed (see, e.g., [11, 25–30]). A line of research examining the neurobiological aspects of resilience and PASTOR (the Positive Appraisal Style Theory of Resilience) is presented in a review article with the comments of 34 different research groups [31]. The model is based on the individual’s assessment of a situation as a central mechanism that leads to an emotional response. Another line of research seeks to identify the protective mechanisms that best explain positive development despite vulnerability [22]. Yet another line puts resilience into a social and cultural context [14, 32]. Here, resilience has been studied in eleven countries, with the development of methods of measurement [33].

In this project, the development of the RESCUR curriculum was based on available scientific evidence, using research on children’s resilience [1, 2]. Moreover, a theoretically well-developed instrument, validated and used in several countries, is used to measure how the level of resilience is affected by implementation of the curriculum.

### Children’s vulnerability

Children who are members a family with relatives with harmful use of alcohol often have a vulnerable everyday life. They run the risks of later ill-health and harmful use of alcohol of their own, and they constitute an exposed and vulnerable group in society [34, 35]. They have a multiplied risk of failure at school, suffer from mental health, and may develop their own harmful use of alcohol and drugs [35]. Therefore, the Swedish government has set as a priority area within the ANDT (alcohol, narcotics, doping and tobacco) strategy to protect children from their harmful effects [36]. The need for effective, well-founded efforts for this group is enormous. Ill-health is twice as high and abuse is 4–5 times as high among the children of addicts as in the rest of the population. There are huge economic savings to make, of 35 billion a year, if ill-health and harmful activity in the group can be reduced to the same levels as those of the rest of the population [37].

Mapping has shown the need for an enhanced child and parent perspective on dependency and addiction care. The children are also a strong driving force for parents with addiction problems seeking treatment and wanting to change their life situation [38]. At the same time, a study of 740,618 children in Sweden has shown that such a family situation is important for children’s schooling and future life [39]. The alcohol-related disorders of both mothers and fathers are associated with the lower school performance of their children at ages 15–16 years. Most of the statistical effects are attributed to the psychosocial circumstances of the family, such as parental psychiatric disorders, drug use and criminality, and the receipt of social or child-welfare interventions.

But we also know that far from all children can get access to the support available in society. Estimates have shown that between 4 and 5% of all Swedish children under the age of 18 live with a parent who has harmful use of alcohol/drugs [40, 41]. Studies at the Center for Health Equity Studies (CHESS) followed children born 1987–89 (*N* = 332,000) up to adulthood, and parents who were abusing or had addiction problems were identified via different registries. A total of 4% of all children had at least one parent who had been treated for harmful use of alcohol (2.5%) and drugs (1.5%) at childbirth [41]. In-depth analysis of the survey from 2012 showed that 56% of these parents want to talk about their parenting, but only 24% of the children living in families where a person was being treated for a dependency disorder was given formal support [42]. A minority of children receiving support already had problems of their own.

Another source of information on support for children in families where at least one parent has harmful use of alcohol/drugs is the report published annually by Junis (IOGT-NTO’s Junior Federation), now in its 12th consecutive year. It is based on surveys of Swedish municipalities, of which 73% participated in 2015 [43]. In 2005, 57% of municipalities had special support groups for children with a parent with harmful use. The proportion was 66% in the report published in 2015. However, in this report, the answers refer not only to support groups but also to individual support. And the number of participants in the various municipalities varied greatly. Conclusions from the different surveys are that there were major regional differences, and that there is a great need for increased efforts to strengthen the child and parent perspective in various parts of social services. Moreover, there is a great need for support for these children as only a small proportion receive formal support.

Accordingly, more actors are needed to offer support, not least non-government organizations. Value-based organizations have the advantage that they have more detailed knowledge of the problems. Junis is an NGO that works with children in Sweden. In addition to working with alcohol and other drugs issues, Junis is concerned with solidarity and democracy issues. Over the country, there are more than 12,000 members aged 6–15 years divided into about 175 local chapters. The organization is run by approximately 1300 voluntary trained leaders. In addition to Junis’s continuous weekly activities, every year throughout the country, a large number of camps are organized, as too are extensive activities in connection with the Christmas and New Year celebrations. Advocacy and education work supporting the needs of children who grow up in a family with harmful use of alcohol and drugs have been important part of Junis’s work plan for more than a decade.

In order to meet these challenges, the present research has been developed using three different complementary approaches: a universal approach through implementation of the curriculum in school classes, a selective approach through groups in the local chapters of Junis, and an indicative approach though groups recruited through the social services as support for the children of alcoholics.

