## Methods/design

### Aims

The primary aims are to strengthen protective factors and promote childhood life changes for 7–14 year-olds who are relatives of people with addiction problems, and to contribute to the support that Swedish society gives to these children. We want to break the pattern of alcohol and drug problems being transmitted between generations. This entails a preventive intervention targeted at those who have an increased risk of developing addiction problems and other problems that are consequences of their situation. A secondary aim at the universal level is to promote protective factors among children of the same ages, and to prevent the development of drug addiction among children.

In order to increase our chances of achieving these goals, we are implementing the project as a collaboration between practitioners and researchers. Our goals also include increasing the relevance of the project, developing knowledge, and improving practical implementation. This can also provide an increased opportunity to disseminate experiences to other groups, and for other activities, after the method has been tested and evaluated based in the Swedish context and in three priority areas – social services, a NGO, and schools.

The research covers five research questions:How can participants in the implementation of the program be recruited?How can leaders be supported to enable the implementation of a high-quality program?What is the significance of the program for children’s development and mental health?Does the program work differently for different groups in relation to gender, social background, place of residence and age?Does the intervention work differently at a universal, selective or indicative level?

The research questions will be studied through an implementation evaluation, using self-assessment forms, interviews and observations using an established “checklist”, as well as through an impact assessment, which has a randomized, controlled pre-post design, in which self-reports, interviews and adult reports of testing instruments are used. Our main target group consists of children aged 7 to 12 years who are in one of the organization’s schools, social services or the value-based organization IOGT-NTO Junior Federation, Junis. A secondary target group consists of the deliverers.

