#### Self-reports from the children

All measures have been translated into Swedish in previous research projects, and the psychometric tests have been shown to work well in the age groups we are evaluating. The instruments that we will use are the following:Child and Youth Resilience Measure (CYRM) [52]. In order to make the evaluation as change-sensitive as possible, we will use the variant with a 5-point Likert scale, instead of the 3-point.How I feel (HIF) [53] is used for older children, and further development of the instrument for younger ages is underway in our EU Comenius Project European Assessment Protocol for Children’s SEL skills [How one feels (HOF)].Health, psychiatric symptoms, somatic symptoms and health behaviors from HBSC (Health Behaviour of School-aged Children) [54, 55],Mastery [56]Demography (gender, age, housing situation, family structure).

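### Research question 5 would read differences between the school, Junis and social-services arms as differences between prevention levels, although level coincides with setting, deliverer, informant and design

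*Protocol article*

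**What the plan says.** Under Children's vulnerability, the protocol article describes three approaches. Schools are universal. The NGO is "a selective approach through groups in the local chapters of Junis". Social services are "an indicative approach though groups recruited through the social services as support for the children of alcoholics". Only the last of these descriptions names a risk on which children are recruited.

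Under Aims, the primary aim concerns "7–14 year-olds who are relatives of people with addiction problems". The next aim reads "A secondary aim at the universal level is to promote protective factors among children of the same ages". Research question 5 asks: "Does the intervention work differently at a universal, selective or indicative level". The same section defines the main target group by age 7 to 12 and by belonging to one of the three types of organisation.

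The Discussion says that question 5 will be answered from pre- and post-measurements by comparing effect sizes between the voluntary organisation, social services and schools, supplemented by leader interviews and observations.

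Participants and recruitment powers the social-services and NGO interventions together as selective groups (d = 0.5, power 0.8, two-sided alpha 0.05, 64 children per group). The universal intervention uses d = 0.3 and 176 per group. For Junis, the section gives recruitment through leaders, 16 groups of about 8 children, and ages 7 to 12.

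**The concern.** Three levels are tied one-to-one to three organisations, so the planned comparison has no contrast in which level varies and the rest stays fixed. A weak result in Junis could be reported as evidence that selective prevention fails, and a strong one in social services as evidence that indicated prevention works. The cause in either case might be the deliverer, the informant or the lack of randomisation.

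The Junis arm adds a second difficulty. The article calls it selective and powers it at the larger effect, but does not say what its children are selected on. A reader cannot tell whether a Junis result bears on the population of the primary aim. The age range of that aim is also wider than that of any arm.

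**Working it through.** **1. What changes together with level.** From Children's vulnerability, Design, Participants and recruitment, Reports from adults, and Data management and analysis:

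| | Schools | Junis | Social services |
|---|---|---|---|
| Level | universal | selective | indicated |
| Deliverer | teachers | Junis volunteers | social workers |
| Adult informant | teacher | group leader | parent first, otherwise social worker |
| Allocation | cluster-randomised by school | not randomised | not randomised |
| Comparison group | waiting-list schools | matched from waiting-list schools | matched from waiting-list schools |
| Entry as described | school years 1 and 4 | membership, age 7–12 | children of alcoholics, ages 7–9 and 9–12 |

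Three arms give two independent contrasts. Between schools and either other arm, every row changes. Between Junis and social services, level, deliverer, informant and entry change. No contrast isolates level, so no model fitted to these arms can separate it. For adult-reported outcomes the problem also lies inside the two non-randomised arms: their children are rated by leaders, parents or social workers, and the matched controls by teachers.

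**2. Is parental risk recorded?** The child measures are a resilience scale, an emotion scale, HBSC health and symptom items, Mastery and background data: "Demography (gender, age, housing situation, family structure"). Adults complete the resilience measure and the SDQ. The Effect study section lists age, gender, residence and problem levels as subgroup factors. None of these is named as a measure of parental alcohol or drug use.

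**3. Reproducing the stated sample sizes.** n per group = 2(z₀.₉₇₅ + z₀.₈₀)²/d², with (1.960 + 0.842)² ≈ 7.849.
- d = 0.5: 2 × 7.849/0.25 = 62.8, so 63; the exact t-test gives 63.8, so 64 as stated.
- d = 0.3: 2 × 7.849/0.09 = 174.4, so 175; the exact t-test gives 175.4, so 176 as stated.

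The arithmetic is sound. What is in question is which effect size applies to the NGO.

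**4. Power if the NGO effect is the universal one.** Power ≈ Φ(d√(n/2) − 1.960), without allowance for clustering or matching.
- 64 per group, d = 0.5: 0.5 × 5.657 = 2.828; Φ(0.868) = 0.81 (t-test 0.80).
- 64 per group, d = 0.3: 0.3 × 5.657 = 1.697; Φ(−0.263) = 0.40 (t-test 0.39).
- 128 per group (the planned 16 × 8 = 128 Junis children and, by assumption, as many matched controls), d = 0.3: 0.3 × 8 = 2.4; Φ(0.44) = 0.67 (t-test 0.67).

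**5. Range over the unknown share at risk.** Assume d = 0.5 in children at risk and 0.3 in the others, so the average is 0.3 + 0.2p for a share p. With 64 per group:

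| p | average d | power |
|---|---|---|
| 4–5% | 0.31 | 0.41 |
| 20% | 0.34 | 0.48 |
| 50% | 0.40 | 0.61 |
| 100% | 0.50 | 0.80 |

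The stated power of 0.80 is reached only if all Junis children carry the risk. The article does not give p.

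**6. Ages.** The primary aim covers 7–14. The target group and Junis cover 7–12, social services 7–9 and 9–12, and schools enrol years 1 and 4. No arm is described as enrolling ages 13–14.

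**The case against.** The strongest objection is that this is a condensed article and the Junis entry rule may stand in a fuller protocol. That has force. A reader might infer that Junis children are not selected at all. The article does not say so: it calls the arm selective, it speaks of recruiting children in all three types of organisation, and its Background names refugees as another group at social risk. That regular volunteers lead the groups describes the leaders, not the children. What can be said is that no criterion is stated.

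A reader might also apply the article's figure that "between 4 and 5% of all Swedish children under the age of 18 live with a parent" with harmful alcohol or drug use, and conclude that only about 5 to 6 of 128 Junis children are in the primary-aim population (128 × 0.04 = 5.1; 128 × 0.05 = 6.4). That step assumes the absence of selection that is in dispute, so it shows one end of a range and nothing more.

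Other stronger readings fail too:
- That Junis is meant to serve the primary aim is only implied. The article ties the secondary aim to the universal level and assigns Junis to neither.
- The reasoning that targeted groups respond more explains the smaller social-services sample. It is not offered for Junis, although d = 0.5 is applied to both.
- That parental use goes unmeasured cannot be asserted, because the HBSC and family-structure items are not shown.

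It is fair to add that the comparison by organisation is openly described, and that moderator analyses, including by problem level, are already planned. This supports a comparison of settings. It does not turn one into a comparison of levels. The range 7–14 might refer to ages reached at the two-year follow-up (12 + 2 = 14), but the Aims section does not say this.

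**Conclusion.** The concern holds in a limited form. On the stated text, question 5 cannot be answered as a question about prevention level: a difference between arms mixes level with organisation, deliverer and adult informant and, where schools are involved, with randomised versus non-randomised design. This does not depend on how Junis children are chosen.

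Only the social-services arm is described as recruited on the risk named in the primary aim, and it is not randomised. For Junis the label and the d = 0.5 have no stated ground. If the universal d = 0.3 applied, power would be about 0.39 with 64 per group, or 0.67 with 128 per group, both ignoring clustering and matching. These figures are conditional illustrations, because the share of Junis children at risk is unknown. The conflict between ages 7–14 and 7–12 is separate and minor, but it too affects whom the conclusions cover.

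The documents do not support saying that Junis children are unselected, or that the arm is shown to be unable to address the primary aim.

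**What to change.** 1. In Aims and in the Discussion, state question 5 as a descriptive comparison of settings, and say that no conclusion about prevention level will be drawn from it.
2. Examine dependence on risk inside the randomised schools, with a prespecified arm-by-baseline-SDQ interaction that respects school-level allocation. This makes the planned analysis by problem level concrete. State that the SDQ measures the child's problems, not parental addiction, and that this baseline is a teacher rating made after schools were allocated.
3. Limit primary-aim conclusions to the social-services arm unless a risk criterion for Junis is documented. If one exists, state it. If not, give another ground for d = 0.5 in the NGO or show power at d = 0.3 beside it.
4. Reconcile the 7–14 and 7–12 age ranges.

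The cost is rewording plus one interaction analysis on data already scheduled for collection. The price is narrower claims and an interaction estimate that will be imprecise.
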